#### Data analysis

For sample characteristics, we will consider descriptive data. For item analysis, we will use descriptive data (N, mean, SD, range, skewness, kurtosis and item difficulty). Internal consistency will be evaluated by Cronbach’s α or the Kuder Richardson coefficient for dichotomous items. To assess test-retest reliability and construct validity, we will calculate correlations. We assume moderate correlations of the modules with related items of the PPEET. With regard to factorial validity, we will perform exploratory factor analysis. Further relevant aspects for reliability and validity testing, for example, additional scales to be used and strengths of correlation, will be determined when the evaluation framework is agreed upon. All data will be analysed using IBM SPSS Statistics 29.^59^ The aim is to obtain a modular tool with internally consistent scales (Cronbach’s α >0.70) that captures a broad spectrum of factors relevant for PPI as identified in the evaluation framework.

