## Objectives

Therefore, the study objectives are (1) To establish a theoretical evaluation framework, (2) Based on this, to develop a modular evaluation tool as a practical questionnaire for various stakeholders and (3) To pilot the modular evaluation tool including psychometric testing.

We would like to prepare an evaluation framework for PPI in health services research in Germany, considering the context, process, outcomes and impacts. The objective of establishing an evaluation framework is related to the following research questions:

What does meaningful and successful involvement in health services research look like for researchers and patients in Germany?How should the evaluation of PPI be approached in health services research in Germany?

We will acknowledge the international literature and will explore the specifics of PPI in health services research in Germany. Items will be devised acknowledging existing instruments as well as qualitative survey and interview data. Related research questions are:

Do the devised items address the consented evaluation framework?Are the devised items of the modular evaluation tool comprehensive and relevant?

The developed modular evaluation tool will undergo validity and reliability testing.

Does the modular evaluation tool produce stable and consistent results?

We will place further emphasis on PPI in the evaluation design and reporting by involving a participatory research team in all phases of the research process.

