### Phase 3: piloting a modular evaluation tool

#### Aim and methods

The pilot study is intended to provide information on the reliability and validity of the developed modular evaluation tool. We will consider the relevant literature on the quality criteria for health outcome measurements.^65 69^ With regard to reliability, we will focus on internal consistency and retest reliability, as there are no measurement standards for PPI evaluation tools. Additionally, we will account for the additional aspects of construct validity: factorial validity and convergent validity.

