##### Web-based pilot study

#### Recruitment and procedures

Researchers and patients will be recruited by updating identifying the principal investigators of ongoing publicly funded health services research. Additionally, snowball sampling and sampling through personal knowledge will be applied. Researchers and patients will be invited to take part in web-based pilot testing of the modular evaluation tool. They will receive emails and individualised links. Reminders will be sent to improve the response rates.^57^ Participants are eligible when they are involved in a currently ongoing health research project that implements PPI. At the end of each survey, participants can also generate a code for specific ongoing projects and send links to the web-based pilot study to identify other project members. The code can be used to merge evaluations on specific projects. Moreover, participants can choose whether they would like to receive a score sheet after closure of the pilot study.

Overall, the pilot study is intended to collect a total of at least 200 responses. Modules that can be answered by researchers or patients only should be answered by at least 100 participants. This will constitute an appropriate sample size providing insights into psychometric testing.^70^ A randomly chosen subsample of n=50 will be invited to fill in the core modules a second time after approximately 1 week. REDCap^58^ will be used to implement the web-based survey. Informed consent will be obtained online.

The survey will include the items from the developed modular evaluation tool items as well as the PPEET^27^ to establish convergent validity. The PPEET has previously been used for validation studies,^29^ and an authorised German version of the PPEET exists. Participating researchers and patients will also be asked to provide information on individual characteristics, such as age and gender, as well as seniority for researchers and patients’ health condition with lived experience for patients, respectively.

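### Retest reliability is to be assessed by correlations, which, unless they are absolute-agreement coefficients, do not register a systematic shift between the two administrations and can overstate stability

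*Protocol article*

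**What the plan says.** The Objectives section of the Protocol article poses a stability question about the tool: "Does the modular evaluation tool produce stable and consistent results". Phase 3, Aim and methods, makes retest one of two reliability aspects: "With regard to reliability, we will focus on internal consistency and retest reliability".

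The design is in Phase 3, Recruitment and procedures: "A randomly chosen subsample of n=50 will be invited to fill in the core modules a second time after approximately 1 week". The parent sample is set there too: "the pilot study is intended to collect a total of at least 200 responses", and for role-specific modules "Modules that can be answered by researchers or patients only should be answered by at least 100 participants". The number 50 comes with no target coefficient, interval width or allowance for non-response. The term for the modules to be repeated is not defined anywhere in the article.

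The analysis is in Phase 3, Data analysis: "To assess test-retest reliability and construct validity, we will calculate correlations". No ICC, agreement measure, analysis of mean change or retest threshold is named. The only reliability threshold concerns internal consistency: "The aim is to obtain a modular tool with internally consistent scales (Cronbach’s α >0.70". The same paragraph defers some detail until the framework is agreed: "Further relevant aspects for reliability and validity testing, for example, additional scales to be used and strengths of correlation, will be determined".

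**The concern.** Construct validity and retest reliability ask different things of a coefficient. Convergent validity asks whether two measures order respondents alike, and a correlation suits that. Retest reliability of a score also asks whether the same respondent gets about the same value again. A Pearson or Spearman coefficient is unchanged if every respondent scores half a standard deviation higher the second time, and a consistency-type ICC removes the occasion effect by construction.

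The level of the score matters for this tool. Pilot participants may ask for a score sheet (Phase 3, Recruitment and procedures). The Dissemination plan foresees an online version for monitoring involvement and giving individual feedback on specific projects. Those uses read the score itself, not only the respondent's rank. An unnoticed shift on repeated completion would be carried into them behind a favourable retest figure.

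Two lesser matters bear on the same conclusion. Fifty is the number invited, so the completed retests will be fewer if anyone declines. And the research question is about the tool, whereas the retest covers only an undefined part of it.

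**Working it through.** **Inputs.** From the Protocol article: 50 retest invitees drawn from at least 200 responses, a correlation as the statistic, and an interval of about one week. Assumed here, because the article gives no figures: a retest correlation of 0.80, mean shifts of 0.25, 0.5 and 0.8 SD, and retest non-response of 20% to 50%.

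**The plan's own figure.** The 50 has no stated derivation, so it cannot be reproduced; only its consequences can be computed.

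**Effect of a shift.** Take two occasions with equal variance (set to 1), correlation r and a mean difference of d SD. The between-person component is r, the error component is 1 − r, and the variance of two occasion means d apart is d²/2. The absolute-agreement single-measure ICC is therefore

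r / (r + (1 − r) + d²/2) = r / (1 + d²/2).

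| Shift d (SD) | 1 + d²/2 | Correlation | Absolute-agreement ICC |
|---|---|---|---|
| 0 | 1.000 | 0.80 | 0.80 |
| 0.25 | 1.031 | 0.80 | 0.8/1.031 = 0.78 |
| 0.5 | 1.125 | 0.80 | 0.8/1.125 = 0.71 |
| 0.8 | 1.320 | 0.80 | 0.8/1.320 = 0.61 |

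A simulation of 400,000 pairs with r = 0.80 and a 0.5 SD shift gave a Pearson coefficient of 0.80, confirming that it does not move.

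**Precision of the retest estimate.** Approximate 95% CI by Fisher's z: tanh(atanh(r) ± 1.96/√(n − 3)), with atanh(0.80) = 1.099.

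- All 50 complete: 1.96/√47 = 0.286, giving 0.67 to 0.88. An F-based interval for an ICC from two ratings also gives 0.67 to 0.88.
- 30 complete (an assumed 60% response): 1.96/√27 = 0.377, giving 0.62 to 0.90.

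**Invitations needed for 50 completed retests.** 50/(1 − non-response), rounded up: 63 at 20%, 72 at 30%, 84 at 40% and 100 at 50%. All of these fit within the planned minimum of 200 responses.

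**Scope.** The Objectives refer to the modular tool as a whole; the recruitment text repeats the core modules only. The two agree if every module counts as core. If any module does not, it has no retest data.

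**The case against.** The strongest reply is that one sentence of a condensed article is being over-read. The word used is generic and plural and does not exclude an intraclass correlation. The type of coefficient is often left to an analysis plan. The deferral clause is introduced by examples and need not be limited to them, and Aim and methods commits to the literature on quality criteria for health outcome measurements. Part of this stands: an absolute-agreement ICC may be what is intended. But the article does state a statistic, and the deferral concerns further aspects and does not reopen it. Even reading it as an ICC leaves the matter open, because a consistency-type ICC also misses a shift.

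A second reply is that the size rests on assumed shifts, with no intervention between administrations about a week apart. That is fair: at 0.25 SD the loss is 0.02, which is negligible.

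Three stronger readings are tempting, and the document does not support them.

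- A reader might infer that researcher-only and patient-only modules get no stability evidence. The core modules are undefined and the tool does not yet exist; role-specific modules may be among them.
- A reader might infer that the retest is too small for each role. No role-specific retest analysis is planned, and a pooled estimate is legitimate if the core modules are common to both roles.
- A reader might infer that a correlation says nothing about stability. It does measure stability of rank order; what it leaves out is agreement in level.

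Nor does the document show that 50 is inadequate. If all complete and reliability is high, the precision is usable.

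**Conclusion.** The point holds, and it is limited. As written, the retest analysis names a statistic that, if Pearson, Spearman or consistency ICC, cannot detect a systematic change in scores. The reported figure could then overstate stability by about 0.02, 0.09 or 0.19 at shifts of 0.25, 0.5 or 0.8 SD from a correlation of 0.80 (0.80 less 0.78, 0.71 and 0.61). These sizes rest on an assumed correlation, assumed shifts and equal variances at both occasions; the article gives no basis for expecting a large shift. The reason to act is that the stated statistic would not reveal a shift if one occurred, and a better one is readily available.

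The other two points are secondary. Fifty is a count of invitees, so the realised interval depends on a response rate that the article does not state. And the stability conclusion can extend only to modules that are actually repeated.

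**What to change.** **Main change, in Phase 3, Data analysis.** State that retest reliability of scale scores will be estimated by a two-way absolute-agreement single-measure ICC with 95% CI, with weighted kappa for single ordinal items, and reported together with the mean change and limits of agreement. Keep correlations for construct validity.

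**Secondary changes, in Phase 3, Recruitment and procedures.**

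- Either state the precision expected from completers (about 0.67 to 0.88 around 0.80 if all 50 complete, 0.62 to 0.90 if 30 do), or send further automated invitations to existing respondents until 50 retests are complete.
- Say which modules count as core, and limit the stability conclusion to the modules retested.

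Inviting every respondent or repeating every module would also work, but those are design preferences that add respondent burden and are not needed to meet this point.

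**Cost.** Slightly more analysis, available in the SPSS software already named; a few more e-mail invitations; and possibly a less favourable coefficient. The Status of the study section says that no substantive work had begun before publication, so the wording can be settled ahead of the pilot.

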### Patient and public involvement

This researcher-initiated study was discussed with participatory research teams and patient advisory boards of previous and ongoing studies. For the proposed 3 year project, a participatory research team comprising eight patient partners will be set up. The first meetings will be used to offer a research training to all patient partners. During the different phases of the project, they will, for example, give feedback on study information and consent forms for the web-based survey, the patient focus groups and the codesign workshop. They will assist in recruiting strategies, discussing qualitative analysis, evaluating cognitive pretests and discussing the proposed findings of this study’s dissemination of project progress and results. Further involvement can be agreed on during the research process. They will assist in writing papers by reviewing early drafts and providing feedback. We plan to involve the participatory research team in all phases of the project through in-person and virtual meetings. Additional feedback from the participatory research team can be obtained via email between the meetings for specific aspects. Members of the participatory research team will be offered an expense allowance to acknowledge their contributions. The participatory process will be continuously evaluated through short surveys after each meeting and systematic reflections on process aspects, for example, team interactions, changes and impacts.^26 27^

## Ethics and dissemination

### Ethical considerations

Researchers and patients will participate in the study. This study does not involve any medical or psychological intervention that poses risk or harm to participants. The study will be conducted in accordance with the principles of the Helsinki Declaration and the standards of good scientific practice. All participants will be informed about the meaning, purpose and procedure of the study as well as the handling of the collected data. Informed consent will be obtained from all participants prior to taking part in the study. Approval from the Local Ethics Committee of the Centre for Psychosocial Medicine, University Medical Centre Hamburg-Eppendorf (LPEK-0889) and data security officer has been obtained (LPEK-0889).

### Data handling

New data will be generated in the empirical parts of the proposed project (survey, interviews). Researchers and patients will provide quantitative (eg, ratings) as well as qualitative data (eg, text, speech) in the web-based surveys, focus groups and co-design workshops. The web-based surveys conducted in phase 1 and phase 3, along with the qualitative review, will use the REDCap. REDCap supports data collection in accordance with the law (ie, DGSVO), protecting the privacy of respondents (eg, secure infrastructure, no cookies, no IP addresses in log files). For transcription of the focus groups, audio recordings will be uploaded to a secure and encrypted network and handled, ensuring data protection regulations. Quality checks of the transcripts will be performed by the interviewers and, if agreed on, by the interviewees. Audio recordings will be deleted after transcription, and the transcripts will be anonymised. Protocols will be made available for those who took part in the workshops or cognitive debriefings. This allows a quality check.

Informed consent for participation in the online surveys, focus groups, co-design workshops, cognitive debriefing and qualitative review will be obtained. The project team will store all data on a secure and encrypted network drive, with access to project team members. Declarations of consent and transcripts or protocols will be archived separately for 10 years before deletion. When compiling the results, no information will be published that could allow conclusions to be drawn about individual persons.

### Dissemination plan

Attention will be given to effectively disseminating project results to researchers and patients. In accordance with open science practices, study deliverables, especially the evaluation framework and the evaluation tool, will be licensed under a creative commons licence and made available on the project website. For both deliverables, patient-friendly accompanying material developed with the participatory research team will be available. After the piloting of the modular evaluation tool, it is aimed at providing an online tool that allows researchers and patients to evaluate PPI in specific projects. This holds the opportunity to monitor PPI in health services research in Germany, but also to enable researchers and patients to receive individual feedback. The implementation of the online evaluation tool will be envisaged for a second funding period.

The study results will be presented to the participating researchers and patients in a public symposium, disseminated at national and international conferences and published in peer-reviewed journals. Moreover, there will be open access to the scientific results (eg, open access articles), and we will provide lay-friendly summaries of published scientific articles on the project website. As is customary, the results will be reported back to the funder on project completion.

### Status of the study

The study started on 1 January 2025, data collection is planned to start on 22 September 2025 and the project is scheduled for completion on 31 December 2027 according to the current timeline. To date, approval from the Local Ethics Committee of the Centre for Psychosocial Medicine, University Medical Centre Hamburg-Eppendorf (LPEK-0889) has been obtained. We have started contacting interested patient partners for the participatory research team and initiated collaborations with international colleagues and cooperation partners. No substantive work within the different study phases has begun prior to the publication of this study protocol.
